### Statistical analysis.

Variables are presented with their frequency distribution. Quantitative variables are summarized by their mean and standard deviation ( $\pm$ SD). All primary analyses were performed on an intention-to-treat basis. Comparison between baseline group characteristics and primary and secondary outcomes for qualitative variables were evaluated by the chi-squared test. For quantitative variables, measures were compared through Student's t test or the nonparametric Mann-Whitney U test if the quantitative variables would not adjust to a normal distribution. The Shapiro-Wilk test was used to verify the normal distribution of data.

Logistic regression analyses were used to assess the effect of the intervention for the primary and secondary outcomes that were significantly different in the univariate analysis. The magnitude of association was evaluated using the odds ratio (OR) and 95% confidence interval (CI). A crude and 5 multivariate models were fitted: model 1 was adjusted for age (continuous) ethnicity and parity; model 2 adjusted for pregestational BMI and gestational weight gain (continuous); model 3 adjusted for gestational, personal and family history, and smoker status (never, current, or former smoker); Model 4 adjusted for the variables in Models 1 and 2; and Model 5, adjusted for the variables in Models 1-3. These models 4 and 5 were only fitted for the primary outcome due to the small number of events in many of the secondary outcome variables.

All *p* values are 2-tailed at less than 0.050. Analyses were done using SPSS, version 21 (SPSS, Chicago, Illinois).

ADENDUM April 01, 2017.

Statistical analysis.

At the suggestion of the statistic ([name]) the crude relative risk has been estimated for each outcome of interest and different methods have been tested for the estimation of adjusted relative risks in cohort studies and clinical trials of common outcomes (1,2,3): a method proposed by Zhan and Yu (2) to correct the adjusted odds ratio in cohort studies of common outcomes and estimate adjusted relative risk and its confidence interval when the incidence of disease is common and adjust for confounding variables exist; the log-binomial model (one of the criticisms of using the log-binomial model for the RR is that it produces confidence intervals that are narrower than they should be, and another is that there can be convergence problems; in our case we have problems of convergence to provide parameter estimates); Poisson regression with robust error variance and Cox regression with robust variance to obtain corrected confidence intervals.

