### Intervention

Eligible women will randomly be assigned to the:

- **Control group (CG).** Women will be assigned to a standard treatment based on recommendations provided in clinical practice. The main recommendation is to reduce all types of fat from both animal and vegetable sources including nuts and EVOO, and a training program is also provided. This prudent diet recommendation represents a contribution of total fat less than 30% of total energy intake (<40 mL EVOO and not nuts consumption), and carbohydrate intake more than 50%. Women will be followed up by the Obstetric Department.
- **Intervention group (IG).** Women with free allotments of EVOO (1 liter/week) and pistachios (150 g/week), and the training program. Dieticians will give personalized

dietary advice to participants with instructions directed to use of EVOO for cooking and dressing, increased consumption of fruit, vegetables, legumes, and fish and avoidance of red or processed meat, butter, cream, fast food, sweets, pastries, and sugar-sweetened beverages. This intervention diet is comprised of an intake of approximately 35-40% of total fat (predominantly unsaturated fatty acids) and 40-45% of low glycemic index carbohydrates, maintaining a protein intake of 20%, similar to the control diet. Nutrition intervention is aimed to achieve a lifestyle score >10 or Nutrition Score >8 based on Diabetes Nutrition and Complications Trial (DNCT) previously reported. The questionnaire is displayed in **Table 1**. Women will be followed up by the Endocrinology Department.

The main investigator will construct a Master Randomization List using a permuted block design. Women will be stratified by age, BMI and parity and allocation will be assigned in a ratio of 1:1 in random blocks of 4 and 6.

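### Randomisation is stratified by age, BMI and parity, but no listed analysis adjusts for all three and still estimates the total effect of the intervention; the cost is modest and conservative

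*Protocol*

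**What the plan says.** **Randomisation (Intervention section).** "Women will be stratified by age, BMI and parity". Women are allotted equally to the two arms, using permuted blocks whose size is either 4 or 6. The cut-points that define the strata are not given.

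**Comparison of outcomes (Final statistical analysis, Statistical analysis).** "Comparison between baseline group characteristics and primary and secondary outcomes for qualitative variables were evaluated by the chi-squared test". No strata are mentioned. The Statistical Analysis section of the original protocol also names a plain chi-squared test for categorical variables.

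**Regression (same part of the Final statistical analysis).** Logistic models are used "for the primary and secondary outcomes that were significantly different in the univariate analysis". Their covariates are fixed:
- Model 1: "model 1 was adjusted for age (continuous) ethnicity and parity".
- Model 2: pregestational BMI and gestational weight gain.
- Model 3: gestational, personal and family history, and smoking.
- "Model 4 adjusted for the variables in Models 1 and 2".
- "Model 5, adjusted for the variables in Models 1-3".

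Models 4 and 5 are kept for the primary outcome, because many secondary outcomes have few events.

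**Addendum of April 2017.** It adds crude and adjusted relative risks by several methods, but does not list the adjustment variables.

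**The concern.** Blocked randomisation within strata forces the arms to be nearly balanced on the stratification factors. If those factors predict the outcome, the difference between arms varies less from trial to trial than it would under simple randomisation. The ordinary chi-squared test does not know this. Its standard error is that of an unstratified trial, so it is too large, the test rejects too rarely under the null, and some power is lost.

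An adjusted analysis would normally recover that precision. Here the listed models do not do so cleanly. Those without weight gain (Models 1 and 3) lack BMI, and Model 3 lists none of the three factors. Those with all three factors (Models 4 and 5) also condition on weight gain. The Secondary outcome section itself lists change in body weight among the quantities to be studied under the intervention. Adjusting for it can remove part of the effect that the trial is meant to measure. In addition, the models are reached only after the conservative test has been significant.

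**Working it through.** **1. Factors against models**

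| Analysis | Age | BMI | Parity | Weight gain after randomisation |
|---|---|---|---|---|
| Chi-squared | no | no | no | no |
| Model 1 | yes | no | yes | no |
| Model 2 | no | yes | no | yes |
| Model 3 | no | no | no | no |
| Models 4, 5 | yes | yes | yes | yes |

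No row has all three factors and no weight gain. The original protocol's rule of selecting covariates at p < 0.15 does not guarantee the factors either.

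**2. The plan's own sample size**

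Inputs (Sample size, Final statistical analysis): control incidence 35%; relative reduction 30%, so 0.35 × 0.70 = 24.5%; difference d = 0.105; two-sided alpha 0.05; power 80%. The mean proportion is 0.2975.

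- Without continuity correction: n = [1.960 × √(2 × 0.2975 × 0.7025) + 0.842 × √(0.35 × 0.65 + 0.245 × 0.755)]² / 0.105² = 296.4, so 297 per group.
- With continuity correction: (296.4 / 4) × [1 + √(1 + 4 / (296.4 × 0.105))]² = 315.2 per group (316 rounded up).

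The stated 315 is reproduced by an unstratified two-proportion formula with continuity correction.

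**3. Power of the uncorrected chi-squared test at 315 per group, ignoring the strata**

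- Null standard error: √(2 × 0.2975 × 0.7025 / 315) = 0.03643.
- Standard error under the alternative: √((0.2275 + 0.1850) / 315) = 0.03619.
- Power = Φ[(0.105 − 1.960 × 0.03643) / 0.03619] = Φ(0.929) = 82.3%.

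**4. Effect of stratified randomisation**

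Let R² be the share of outcome variance explained by the strata. The protocol gives no value. The Background calls maternal obesity a major risk factor for GDM but gives no strength, and it says nothing comparable for age or parity. R² is therefore an assumption, shown over a range. With s = √(1 − R²), the true sampling standard deviation is s times the unstratified one.

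- Type I error of chi-squared: 2 × [1 − Φ(1.960 / s)].
- Power of chi-squared: Φ[(0.105 − 1.960 × 0.03643) / (0.03619 s)].
- Power of a stratified test: Φ[(0.105 − 1.960 × 0.03643 s) / (0.03619 s)].

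| R² (assumed) | Standard error too large by | Type I error, chi-squared | Power, chi-squared | Power, stratified | Points given up |
|---|---|---|---|---|---|
| 0 | 0% | 5.0% | 82.3% | 82.3% | 0 |
| 0.01 | 0.5% | 4.9% | 82.5% | 82.7% | 0.3 |
| 0.02 | 1.0% | 4.8% | 82.6% | 83.1% | 0.5 |
| 0.05 | 2.6% | 4.4% | 83.0% | 84.2% | 1.3 |
| 0.10 | 5.4% | 3.9% | 83.6% | 86.1% | 2.5 |
| 0.15 | 8.5% | 3.4% | 84.3% | 88.0% | 3.7 |

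**5. Check by simulation**

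2,500 trials per scenario, 630 women, eight strata (three binary factors with assumed prevalences of 50%, 30% and 50%), permuted blocks of 4 and 6, ordinary chi-squared against Mantel-Haenszel.

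| Assumed odds ratios (age, BMI, parity) | R² | Type I error, chi-squared / stratified | Power, chi-squared / stratified |
|---|---|---|---|
| 1, 1, 1 | 0 | 4.6% / 4.7% | 82.5% / 82.4% |
| 1.5, 1.5, 1.2 | 0.02 | 4.5% / 4.6% | 83.1% / 83.4% |
| 2, 2.5, 1.5 | 0.07 | 4.0% / 5.0% | 83.4% / 85.2% |
| 3, 3, 2 | 0.13 | 3.1% / 4.8% | 83.7% / 86.4% |

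Monte Carlo error is about 0.4 points for type I error and 0.7 for power. The simulation agrees with the formulas within that error.

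**The case against.** The other side has a good case on weight.

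- **The test errs in the safe direction.** Type I error does not exceed 5%, and an unadjusted comparison after stratified randomisation is valid, only inefficient. This stands.
- **The plan's power is not breached.** The sample size was computed for an unstratified comparison, and chi-squared power stays near 82% to 84% at 315 per group. It is 86.1% at the 350 per group implied by the expected 700 women assessed, even ignoring the strata. This stands. A reader might infer that the mismatch leaves the trial underpowered; the documents do not support that. The loss is relative to a matched analysis.
- **The strength of the strata is unknown.** Only obesity is documented as a risk factor, and the cut-points are missing. This stands, so the size can only be given as a range that includes zero.
- **Models 4 and 5 do contain all three factors.** This is true, and a reader who infers that the factors are never adjusted for would be wrong. The objection to these models is specific: they add a variable that arises after randomisation, so they do not estimate the total effect. They are also fitted only for the primary outcome, and only if the univariate test is significant.
- **No section calls the chi-squared test the primary analysis.** True, and the regressions are described as the means of assessing the effect. But because they are conditional on the univariate result, the chi-squared test is the first and deciding comparison.
- **An oversized standard error is not a property of every measure.** Correct. It applies to the chi-squared test and the crude risk difference. In logistic regression, adjustment need not shrink the standard error of the log odds ratio; the gain comes through a larger conditional effect.

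**Conclusion.** The mismatch is real and rests on the text alone: three stratification factors, an unstratified deciding test, and no listed analysis that adjusts for all three without also conditioning on weight gain.

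Its consequence is modest and conditional. If the strata explain 1% to 15% of outcome variance (an assumption), the chi-squared test runs at a true level of about 4.9% to 3.4% and gives up about 0 to 4 points of power, with power still above 80%. If they explain nothing, there is no loss. One might read the oversized standard error as a threat to the validity of a positive result. It is not, because the error is conservative. The point is an improvement in efficiency and in the match between design and analysis, not a correction of a misleading test.

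**What to change.** Make the primary analysis one of the following:
- a Mantel-Haenszel analysis of GDM by the strata used in the randomisation list; or
- the relative-risk regression already named in the April 2017 addendum (Poisson with robust variance), adjusted for baseline age, pregestational BMI and parity.

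In either case, leave gestational weight gain out and do not make the analysis depend on a significant univariate test. Keep the crude chi-squared test as supportive. Use the same three baseline factors for secondary binary outcomes where event numbers allow. State the cut-points that define the strata.

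The cost is a sentence or two in the analysis section and one re-run. No new data are needed: age, parity and pregestational BMI are already covariates in the listed models, and the strata are fixed by the randomisation list.

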### **Secondary outcome:**

- To define functional genetic risk of developing GDM focusing in obese and non obese pregnant women.
- To investigate the effects of MedDiet and physical exercise/activity scheduled in inflammatory biomarkers in pregnant women.
- To investigate the effects of MedDiet and physical exercise/activity scheduled in the epigenetic mechanisms (DNA methylation and miRNA expression) in pregnant women and offspring; if so, it would represent a novel epigenetic mechanism for regulation of gene expression in the offspring.
- To investigate whether the MedDiet and physical exercise/activity scheduled alters the composition of the gut microbial flora both in women and offspring.
- To evaluate the impact of all these parameters on the long-term health of newborns in the first year of life.
- To estimate changes in HbA1c, insulin, HOMA, lipid profile, body weight, blood pressure, adherence to changes in lifestyle estimated by Med Score and urinary hydroxytyrosol levels and plasma  $\gamma$ -tocopherol levels to confirm compliance in the group receiving MedDiet [extra virgin olive oil (EVOO) and pistachios].
- The parameters to be assessed will be: gestation duration and fetal development; delivery characteristics such as caesarean delivery and instrumental vaginal birth, placental weight; and newborn data such as newborn weight, Apgar test values and cord blood pH.

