## **STATISTICAL ANALYSIS**

Analysis of all the variables pertaining to efficacy will be performed on an intention-to-treat basis, including data on all patients randomized and all available follow-up data.

The Student's t test or ANOVA [nonparametric test (RANK TEST)] will be used to compare continuous variables [and expressed as means standard deviation (SD)] while categorical variables will be compared using the chi-squared test. The association between qualitative variables will be analyzed by the chi-squared test or Fisher's exact test in case more than 25% of the expected values will be less than five. In the case of ordinal variables, the hypothesis of ordinal proportion tendency will be tested.

Relative risk will be assessed together with its 95% confidence interval, using Cornfield's method. In all cases, the distribution of the variable versus the theoretical models will be checked, and the variance homogeneity hypothesis will be tested. The paired Student's t test or a repeated measures analysis of variance (MANOVA) will be used to compare continuous variables. The changes in variables with time (pre- and post-treatment) will be estimated by a MANOVA. Variables included will be treatment and study period. Mathematical models will be chosen by the type of variable and used logistic analysis, linear regression or Cox regression. The existence of interactions will be evaluated. Variables showing a p value under 0.15 in the univariate analysis will be selected for the multivariate analyses. The null hypothesis will be rejected in each statistical test when  $p < 0.05$ . Analysis will be performed using windows SPSS version 17.0 software and STATA 12.

Interim analyses: No applicable.

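### The final analysis gives continuous secondary outcomes an unadjusted test only; every effect estimate with an interval, and every adjusted model, is an odds ratio or relative risk that does not fit them

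*Protocol*

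**What the plan says.** Under Objectives, Secondary outcome, the protocol sets out to estimate changes in metabolic measures (HbA1c, HOMA, insulin, lipids, blood pressure, body weight). It also lists gestation duration, placental weight and "newborn data such as newborn weight, Apgar test values and cord blood pH". The only outcomes named there that are binary by nature are caesarean and instrumental vaginal birth.

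The earlier section, Statistical analysis, fits the method to the outcome: "Mathematical models will be chosen by the type of variable and used logistic analysis, linear regression or Cox regression". It also plans MANOVA for change over time, with treatment and study period as terms.

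The later section, Final statistical analysis, works in two steps.

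- Step 1, univariate: "For quantitative variables, measures were compared through Student's t test or the nonparametric Mann-Whitney U test", the choice depending on normality. Qualitative variables go to the chi-squared test.
- Step 2, effect and adjustment: "Logistic regression analyses were used to assess the effect of the intervention for the primary and secondary outcomes". This step is restricted to outcomes whose step 1 comparison reached significance. For the effect measure the text says "The magnitude of association was evaluated using the odds ratio (OR) and 95% confidence interval (CI". One crude and five adjusted models follow. Models 4 and 5 are kept for the primary outcome, "due to the small number of events in many of the secondary outcome variables".

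The addendum of April 01, 2017 says that "the crude relative risk has been estimated for each outcome of interest" and lists methods for adjusted relative risks.

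**The concern.** Step 2 covers secondary outcomes without being restricted to binary ones, and it is the only place where the final text names an effect measure with an interval or an adjusted model. An odds ratio or relative risk cannot be fitted to HbA1c, newborn weight or cord pH on its measured scale. Followed literally, the plan therefore tests these outcomes and then either stops or sends them to a model that cannot take them.

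What is at stake is the stated aim of estimating changes. A p value does not say how many grams, mmHg or pH units separate the groups, or how precisely that is known. The outcomes measured before and after the intervention also lose any use of the baseline value. And because step 2 depends on a significant univariate test, a non-significant outcome gets no interval showing which differences the data rule out.

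**Working it through.** **Side by side**

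| | Earlier section (Statistical analysis) | Final statistical analysis and April 2017 addendum |
|---|---|---|
| Test of a continuous outcome | t test, ANOVA or rank test | t test or Mann-Whitney |
| Change over time | MANOVA, paired t test | none named |
| Regression for a continuous outcome | linear regression | none named |
| Effect measure with CI | relative risk | odds ratio; relative risk |
| Adjusted model | by type of variable | logistic; adjusted relative-risk methods |
| Which outcomes reach the model | covariates selected at p < 0.15; outcomes not filtered | outcomes significant in the univariate test (logistic models) |

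So the final text names neither a mean difference with CI nor an adjusted model for any continuous outcome. This needs no numerical assumption.

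**The plan's own figure.** Inputs from Sample size: 35% against 0.70 × 35% = 24.5%, two-sided 5%, 80% power. With mean proportion 0.2975 and difference 0.105:

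n = [1.960 √(2 × 0.2975 × 0.7025) + 0.842 √(0.35 × 0.65 + 0.245 × 0.755)]² / 0.105² = 296.4, so 297 per group.

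With the continuity correction, (n/4)[1 + √(1 + 4/(n × 0.105))]² = 315.2, or 316 rounded up. The stated 315 is reproduced and is used below.

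**What the missing interval would look like.** For a continuous outcome with 315 per group, the unadjusted 95% CI for the mean difference has half-width 1.960 × √(2/315) = 0.156 SD. With 350 per group (half of the 700 the protocol expects to assess) it is 0.148 SD. Adjusting for a baseline value correlated r with the outcome multiplies the residual variance by about 1 − r². The documents give no r.

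**What cutting would cost, if it were done.** The documents give no SD, effect size or cut point for any secondary outcome. Assume a normal outcome and a pure mean shift.

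1. Shift with 80% power uncut: d = (1.960 + 0.842) × √(2/315) = 0.223 SD.
2. If a share q of controls lies above the cut, then c = z(1 − q), and the share in the other group is 1 − Φ(c + d) for a reduction or 1 − Φ(c − d) for an increase.
3. Example with q = 5%: c = 1.645, so the other group has 3.1% or 7.8%. Controls contribute 0.05 × 315 ≈ 16 events.
4. Power of the two-proportion test at 315 per group, with asymptotic efficiency φ(c)²/[q(1 − q)]:

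| Controls above the cut | Power after the cut (reduction – increase) | Relative efficiency |
|---|---|---|
| uncut | 80% | 1 |
| 50% | 60.5% | 0.64 |
| 20% | 46.8 – 52.4% | 0.49 |
| 10% | 33.6 – 40.5% | 0.34 |
| 5% | 22.9 – 29.3% | 0.22 |

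With 350 or 500 per group, and d reset to 80% power each time, the results agree within about 1 point.

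**The case against.** The strongest reply is that the plan does analyse continuous outcomes uncut. The t test and Mann-Whitney test use every measured value, the unadjusted t test is valid in a randomised trial, and means with SDs are to be reported, so a reader can derive a crude difference and an approximate CI. This stands. It limits the point to estimation and adjustment.

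A reader might infer more: that because logistic models are applied to secondary outcomes and few events are mentioned, newborn weight, HbA1c and the rest were dichotomised, with the power losses tabulated. The documents do not support that. No section states a cut point or says that a continuous outcome is cut. The remark on few events also fits outcomes that are binary by nature, and the protocol's perinatal lists are open-ended. The logistic step follows univariate tests that run on the full scale.

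It can also be said that the April 2017 relative risks are meant for binary outcomes, as the binary-data methods cited there suggest, and that the earlier section was never revoked, so linear regression may still be intended. Both are possible. But the final text does not say either, and its heading presents it as the final analysis.

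Lastly, model detail for each secondary outcome commonly belongs in a statistical analysis plan that is not shown here. That would answer a complaint about silence. Here the protocol itself fixes tests, models, covariate sets and effect measures, and what it fixes does not fit most of the outcomes it names.

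**Conclusion.** The point holds as a gap in estimation. In the final analysis, continuous secondary outcomes have an unadjusted test, no specified mean difference with CI and no adjusted estimate, while the only effect measures with intervals suit binary outcomes. This rests on the text alone.

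The fall in power from 80% to between 60.5% and about 23% is conditional. It applies only to an outcome that is dichotomised to fit the logistic model, and assumes normality, a pure mean shift and 315 per group. As the plan is written, the univariate test incurs no such loss. The primary outcome is not affected. This is a free improvement: a better method is available on data the trial already collects.

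**What to change.** In Final statistical analysis, reinstate the earlier section's rule that the model follows the type of variable, and say how the two sections relate.

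- For every continuous secondary outcome, whether or not its univariate test is significant, report the between-group mean difference with 95% CI from a linear model on treatment. Adjust for the baseline value where one was measured, and for baseline covariates, for example the stratification factors age, BMI and parity.
- Restrict the logistic models, odds ratios and relative risks (including those in the April 2017 addendum) to binary outcomes.
- Restrict the small-number-of-events reason for withholding Models 4 and 5 to binary outcomes. It is no reason to leave a continuous outcome unadjusted.
- If any continuous measure is also to be shown as a category, state the cut point and present it as a supplement.

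The cost is a few extra regressions and table columns. No added women, visits or measurements are needed.

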## Final statistical analysis

### Sample size

For sample size calculation the primary end-point was the incidence of GDM between 24-28 GWs. We estimated that 315 women per group would be required to provide statistical power of 80% (2-tailed  $\alpha = 0.05$ ) to detect a relative risk reduction of at least 30% after intervention assuming an incidence of 35% GDM in the control group. Previously, this intervention has shown a decrease of the median of fasting blood glucose (FBG) -0.38 mmol/L after 3 months, representing a potential reduction of GDM rate higher than 30%. Taking into account loss to follow-up, we included 1000 successive women that attended their first ultrasound visit at the Obstetrics department between 12-14 GW, to guarantee a minimum duration of 12-weeks of intervention.

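### Adjusted effects for secondary outcomes are fitted only where the univariate test was significant, so those reported are biased away from the null

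*Protocol*

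**What the plan says.** Three places in the protocol bear on this.

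- **Final statistical analysis, Statistical analysis.** Groups are first compared by univariate tests, with p "values are 2-tailed at less than 0.050". Logistic regression is then used to assess the intervention "for the primary and secondary outcomes that were significantly different in the univariate analysis". Effects are expressed as an odds ratio (OR) with 95% CI from a crude model and five adjusted models. The covariates are named in advance: "model 1 was adjusted for age (continuous) ethnicity and parity; model 2 adjusted for pregestational BMI and gestational weight gain (continuous"), then "model 3 adjusted for gestational, personal and family history, and smoker status". Models 4 and 5 combine these sets and were "only fitted for the primary outcome due to the small number of events in many of the secondary outcome variables".
- **Addendum of April 01, 2017.** This reports that "the crude relative risk has been estimated for each outcome of interest" and that several methods for adjusted relative risks were tried. It does not say for which outcomes adjusted relative risks are given, and it does not withdraw the significance condition.
- **STATISTICAL ANALYSIS, before the addenda.** A different covariate rule stands here: "Variables showing a p value under 0.15 in the univariate analysis will be selected for the multivariate analyses". It is not marked as replaced by the named models.

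**The concern.** A rule that fits the effect model only after a significant test lets the result decide whether the estimate exists. When power is low, an estimate can pass only if chance has pushed it well beyond the true effect. The adjusted effects that survive are then too large on average, and their nominal 95% intervals can miss the truth too often. Outcomes that fail the test get no adjusted estimate, so a reader cannot see adjusted results compatible with no effect.

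The trial is sized on the primary outcome alone, and the protocol concedes sparse events in many secondary ones. Low power is therefore the expected situation for outcomes such as instrumental delivery. What is at stake is how much credit maternal and newborn findings receive.

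**Working it through.** **Inputs from the protocol.** Control incidence of gestational diabetes 35%; relative reduction 30%, so 0.70 × 35% = 24.5%; two-sided alpha 0.05; 80% power; 1:1 allocation; 1000 randomised (500 per group), with at least 700 expected to be assessed (350 per group).

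**Assumptions.** No secondary event rates or effects are given. I take control rates of 2%, 5%, 10% and 20%, each with a true relative risk of 0.70.

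**Step 1: the plan's own figure.** The protocol states that "315 women per group would be required to provide statistical power of 80"%. With mean proportion 0.2975 and difference 0.105:

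n = [1.960 × √(2 × 0.2975 × 0.7025) + 0.842 × √(0.35 × 0.65 + 0.245 × 0.755)]² / 0.105² = 296.4, so 297.

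With continuity correction: (296.4 / 4) × [1 + √(1 + 4 / (296.4 × 0.105))]² = 315.2, which agrees with 315. The primary inputs are reproduced.

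**Step 2: what an estimate must reach to pass.** Roughly, |log OR| must exceed 1.96 × SE, with SE = √(1/a + 1/b + 1/(n−a) + 1/(n−b)). At expected counts and 350 per group:

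- 5% v 3.5% (17.5 and 12.25 events): SE = 0.380, so the OR must be below exp(−0.746) = 0.47. The true OR is 0.689.
- 10% v 7% (35 and 24.5 events): SE = 0.275, so below 0.58. The true OR is 0.677.
- 20% v 14% (70 and 49 events): SE = 0.204, so below 0.67. The true OR is 0.651.
- Primary, 35% v 24.5% (122.5 and 85.75 events): SE = 0.167, so below 0.72. The true OR is 0.603.

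In the first two cases the truth itself would not pass, so a passing estimate in the right direction must overshoot. In the last two the truth passes and the filter removes less.

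**Step 3: simulation.** 400,000 two-arm trials per row, keeping those with chi-squared p < 0.05. Among those kept, the table gives the geometric mean OR, the ratio of the mean log OR to the true log OR, and the coverage of the Wald 95% CI. Tables with a zero cell are dropped.

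| Rates | n per group | True OR | Passes | Mean OR if passed | Inflation of log OR | Coverage |
|---|---|---|---|---|---|---|
| Primary, 35% v 24.5% | 315 | 0.603 | 82.5% | 0.569 | 1.11 | 97.0% |
| | 350 | 0.603 | 86.2% | 0.576 | 1.09 | 97.1% |
| | 500 | 0.603 | 95.5% | 0.594 | 1.03 | 97.5% |
| 20% v 14% | 350 | 0.651 | 56.3% | 0.562 | 1.34 | 95.8% |
| | 500 | 0.651 | 71.6% | 0.599 | 1.20 | 96.6% |
| 10% v 7% | 350 | 0.677 | 29.5% | 0.485 | 1.86 | 92.3% |
| | 500 | 0.677 | 39.8% | 0.538 | 1.59 | 94.1% |
| 5% v 3.5% | 350 | 0.689 | 16.6% | 0.377 | 2.62 | 85.6% |
| | 500 | 0.689 | 21.4% | 0.437 | 2.22 | 89.3% |
| 2% v 1.4% | 350 | 0.696 | 8.0% | 0.223 | 4.14 | 86.1% |
| | 500 | 0.696 | 10.8% | 0.280 | 3.51 | 82.9% |

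Without the filter the same scenarios are nearly unbiased (for example OR 0.680 against 0.689 at 5% and 350 per group), with coverage of 95% to 97%.

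The crude OR stands in for the adjusted OR here. Under randomisation the two move closely together, so selection on one carries over to the other.

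**Step 4: the p < 0.15 covariate rule.** This was checked separately in 4,000 simulated randomised trials of 700 women with eight assumed baseline covariates (log OR per SD 0.4, 0.3, 0.2, 0.1 and four zeros). Mean log OR was −0.508 with screening and −0.512 with all covariates fixed, for a truth of −0.506. Coverage was 95.3% and 95.0%; under no effect it was 94.0% and 93.8%. The screen did no harm to the treatment estimate.

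**The case against.** The strongest reply is the April 2017 addendum. A crude relative risk is estimated for every outcome without a significance condition, and in a randomised trial that is a valid effect estimate. A reader might infer from the logistic sentence that non-significant outcomes get no effect estimate at all; the addendum shows otherwise. This part of the reply stands. It leaves the adjusted effects untouched, because the addendum neither removes the condition nor says that adjusted relative risks cover every outcome.

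Three other stronger readings also fail.

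- **Under-coverage for the primary outcome.** At the planned effect, conditional coverage is 97.0% to 97.5%. The qualifying clause may also attach to the secondary outcomes alone, since Models 4 and 5 are described for the primary outcome without condition.
- **Exaggeration through the p < 0.15 rule.** The rule is absent from the Final statistical analysis, which names its covariates, and Step 4 found no bias or loss of coverage from it.
- **Near-zero coverage when there is no true effect.** At a 5% rate it is 8.5% (350 per group) or 4.3% (500 per group). This is almost a tautology: a significant test nearly always means that the interval excludes the null, in any trial.

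It is also fair to say that every outcome is still tested, and that neither the primary test nor its type I error is affected.

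**Conclusion.** The point holds for the adjusted effects of secondary outcomes. With assumed control rates of 5% to 10%, relative risk 0.70 and 350 to 500 women per group, reported log ORs are inflated about 1.6- to 2.6-fold with 86% to 94% coverage. At 2% the inflation is 3.5- to 4.1-fold. At 20% it is 1.2- to 1.3-fold and coverage is intact. These sizes depend on the assumed rates and effect and on the crude OR as proxy; the direction does not.

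For the primary outcome the numerical distortion is small: 3% to 11% on the log-OR scale, with no under-coverage. What remains there is procedural. On one reading of the sentence, a non-significant crude test would leave no adjusted primary estimate.

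The two covariate rules are an inconsistency to tidy up, and nothing shows that they bias the result.

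**What to change.** - In the Final statistical analysis, delete the condition that limits logistic models to outcomes significant in the univariate analysis.
- Fit the same pre-named adjusted model to the primary outcome and every listed binary secondary outcome, and report the estimate and 95% CI whatever the univariate p value.
- Where events are few, state in advance a shorter set of baseline covariates, for example the stratification factors age, BMI and parity.
- State in the April 2017 addendum that adjusted relative risks, like the crude ones, are given for every outcome.
- Mark the p < 0.15 sentence in the earlier STATISTICAL ANALYSIS section as superseded by the named models.

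The cost is a few more table rows, some imprecise estimates for sparse outcomes, and some results that look less favourable. No new data are needed.
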